## Abstract

**Background:**

Injuries to digital nerves in the hand are very common and result in sensory disturbances, which can have a major negative impact on hand function. The gold standard of treatment is end-to-end nerve repair with sutures, at the latest within 2 weeks from injury. Despite operative treatment of digital nerve injuries, the clinical results are often poor. Recent literature questions the evidence supporting surgical repair of digital nerve injuries in adults.

**Methods:**

In this randomized controlled trial, we will allocate patients with injury to a single digital nerve to either surgical nerve repair and cast, or immobilization only. The primary outcome is the return of sensation, measured as static two-point discrimination, at 12 months after injury. Secondary outcomes include complications, the Semmes–Weinstein monofilament test, the Mini Sollerman hand function test, and patient-reported outcome measures.

**Discussion:**

The lack of high-quality studies comparing surgical repair of digital nerve injuries to simple immobilization of the finger motivates the conduct of this randomized study.

**Trial registration:**

ClinicalTrials.gov. TRN: NCT05536609. Registered on 08/23/2022.

**Supplementary Information:**

The online version contains supplementary material available at 10.1186/s13063-026-09956-1.

## Introduction

### Background and rationale {6a}

The digital nerves in the palm and fingers are the most frequent locations for peripheral nerve injuries [1]. The incidence is approximately 6.2–8.3/100.000 person-years [2, 3]. Hand function is essential for almost every activity, and a nerve injury with sensory loss or painful hyperesthesia can have a major negative impact on a person’s life. The need for adaptation of daily activities and the inability to perform previous work tasks, resulting in sick leave, have consequences for both the individual and society [3].

Despite surgical repair of nerve injuries, the clinical results can be poor [4]. Limited recovery of sensory function, development of cold intolerance, and painful neuroma in the affected finger are some of the remaining problems involved. A 2019 systematic review on the surgical repair of digital nerve injuries concluded that there is weak evidence to support digital nerve repair in adults with isolated digital nerve injuries [4]. A retrospective cohort study comparing sutured to non-sutured digital nerves found no difference in sensory recovery in groups with injuries distal to the middle of the middle phalanx [5]. A recently published randomized controlled study compared suture repair of digital nerve injury to alignment of the nerve ends. Results do not support beneficial effect of suture repair [6]. No randomized controlled study comparing operative treatment with immobilization alone has yet been published.

## Objectives {7}

The primary objective of this study is to investigate whether the return of static two-point discrimination (S2PD) after non-operative treatment is inferior to surgical repair of isolated digital nerve injury at 1-year follow-up.

Secondary objectives include comparison between the two groups for differences in patient-reported outcomes and hand function, including range of motion, grip strength, and additional aspects of sensation. We will also investigate complications and sick leave.

## Trial design {8}

This is a single-center, unblinded, superiority, randomized controlled trial. The study includes patients with isolated digital nerve injuries, defined as a single digital nerve laceration without concomitant injury to flexor or extensor tendons, or to adjacent digital nerves. Patients will be randomized in a 1:1 ratio, without stratification, to either surgical nerve repair and cast, or immobilization only.

## Methods: participants, interventions and outcomes

### Study setting {9}

The Department of Hand Surgery at Södersjukhuset Stockholm, Sweden, covers all specialized hand surgery, including nerve repairs, in the capital of Sweden. The catchment area has a population of approximately 2.5 million.

### Eligibility criteria {10}

Patients presenting with a suspected digital nerve injury will be referred to and examined at the Department of Hand Surgery at Södersjukhuset by the on-call surgeon, according to standard procedure. The eligibility criteria for this study will be assessed during the examination.

### Inclusion criteria

Sharp cut, isolated single digital nerve injuryLevel of injury at the proximal or middle phalanx ≥20 years of age at the time of injuryTreatment/surgery possible within 10 days from injury

### Exclusion criteria

Suspected concomitant tendon injury or fracture.Injury to the digital nerves in the thumb.Ongoing wound infection.Chronic neurological conditions.Cognitive disabilities and dementia.Ongoing drug or alcohol abuse.Injury > 7 days at examination

### Who will take informed consent? {26a}

At the time of examination, participants will receive both written and oral information about the study presented by either the on-call surgeon or a nurse. If the patient agrees to participate in the study, written informed consent will be obtained prior to enrollment.

### Additional consent provisions for collection and use of participant data and biological specimens {26b}

This study will not involve the collection of biological specimens, nor will participant data from this study be used in any ancillary studies.

## Interventions

### Explanation for the choice of comparators {6b}

There are no published randomized studies comparing results after surgical nerve repair to non-operative treatment of digital nerve injuries. Nevertheless, in 2025, the gold standard for treating digital nerve injuries is surgical treatment. A review study from 2019 was not able to show superior results in favor of either treatment of digital nerve injuries [4]. A non-randomized comparative study from 2023 reported improved S2PD following nerve repair in injuries proximal to the middle level at the middle phalanx. However, it found no significant differences in outcomes for sharp/dull or warm/cold sensation discrimination, complication rates, or patient-reported satisfaction [5]. In a recently published randomized controlled study, participants were randomized to either perioperative nerve suture or nerve alignment. The trial was closed early owing to a slow recruitment rate and therefore did not reach the intended sample size. However, the available data did not find one treatment superior to the other [6].

In this study, patients are randomized to either surgical nerve repair and cast immobilization or to cast immobilization alone, as both approaches are currently considered possible treatment options.

### Intervention description {11a}

At first examination, eligibility criteria, demographics, and information regarding the injury and its extent (perceived gender, date of birth, smoking, dominant hand, injured hand, profession, date of injury, injury mechanism, injured finger, injured nerve (ulnar/radial), level of injury (proximal or middle phalanx)) will be registered. Clinical examination will include sensory evaluation with S2PD of both the injured and the contralateral finger, as well as measurement of the distance between the injury and the fingertip in millimeters. Participants will be randomized to either nerve repair and cast or cast immobilization alone.

### Intervention group

Nerve repair will be performed under local, regional, or general anesthesia. The nerve will be repaired under loupe magnification, with epineural sutures using 8.0–9.0 nylon. Postoperative cast immobilization will be maintained for 3 weeks. The level of experience of the treating surgeon may range from that of a resident to that of a senior specialist.

### Control group

Cast immobilization will be maintained for 3 weeks. The cast will be administered by a nurse on the day of allocation.

In both groups, immobilization will consist of a cast over the wrist, stabilizing the metacarpophalangeal (MCP) joints in flexion and the proximal interphalangeal (PIP) joints in extension. Fingertips are left exposed to allow for sensory relearning exercises. Adjacent uninjured fingers will be included in the cast depending on the injury site and surgeon’s preference.

The follow-up protocols will be identical for both groups. All participants will be referred to an occupational therapist specialized in nerve rehabilitation to initiate early sensory relearning within 0–4 days following inclusion in the study. At 3 weeks, the cast and sutures will be removed. At this time, the occupational therapist will evaluate finger movement, sensation, strength, and overall hand function using standardized assessments, including active range of motion (AROM), S2PD, Semmes–Weinstein monofilament test (SWM), temperature and sharp/dull discrimination, the Mini Sollerman test, grip strength using the Jamar dynamometer, and Key pinch strength using the Pinch gauge. Follow-up evaluations will be conducted at 3, 6, and 12 months after inclusion (Table 1).

**Table 1 Tab1:** COPS trial participant timeline

	Study period							
	Enrolment	Allocation	Post allocation/surgery					Close out
**Timepoint**	*-t*_*1*_	0	0–4 days	3 weeks	3 months	6 months	12 months	> 12 months
**Enrolment**								
Eligibility screen	X							
Informed consent	X							
Inclusion protocol		X						
Randomization surgery + cast or cast only		X						
**Intervensions**								
Sensory education			X					
Removal of cast and sutures				X				
**Assessments**								
Distance Injury—fingertip (mm)		X						
S2PD (mm)		X		X	X	X	X	
AROM (degrees)				X	X	X	X	
SWM (filament)				X	X	X	X	
Temperature (cold/warmth)				X	X	X	X	
Sharp/Dull				X	X	X	X	
Mini Sollerman test (points)				X	X	X	X	
Grip strength (kg) + VAS (0–10)				X	X	X	X	
Key pinch (kg) + VAS (0–10)				X	X	X	X	
**PROMs**								
Quick DASH		X			X	X	X	
HQ-8 before op		X						
HQ-8					X	X	X	
HADS		X						
PCS		X						
DN4				X	X	X	X	
**Other parameters**								
Demographics^a^	X							
Signs of infection (Yes or No)	X		X	X	X	X	X	
Sick leave (days)							X	

^a^Age, gender, smoking, handedness, occupation, comorbidities, injury mechanism, level of injury, time from injury to operation/immobilization

Participants will also receive general information about nerve injuries and rehabilitation, such as guidance on managing cold sensitivity and exercises to prevent finger stiffness. Patient-reported outcome measures (PROMs) focusing on hand function, pain, and psychological aspects will be collected (Table 1).

### Criteria for discontinuing or modifying allocated interventions {11b}

All participants are free to withdraw from study participation at any time. If any complications such as stiffness, infection, or pain should occur, they will be treated according to local routines. All results will be presented according to the intention-to-treat principle.

### Strategies to improve adherence to interventions {11c}

To improve adherence to the study protocol, the participants will be scheduled for all visits pertinent to the study follow-up. Questionnaires will be filled out during follow-up visits. If there are any questions, occupational therapists or other health care personnel will be available to assist with instructions. Participants who fail to attend follow-up visits will be contacted by phone or mail.

### Relevant concomitant care permitted or prohibited during the trial {11d}

No data or biological specimens from this study will be used in ancillary studies.

### Provisions for post-trial care {30}

Participants will not receive any compensation for their involvement in the study. The patients are covered by the Swedish patient injury insurance, Landstingets Ömsesidiga Försäkringsbolag (LÖF).

### Outcomes {12}

#### Primary outcome

Primary outcome measures will be collected at 12 months after injury.

### Static Two-Point Discrimination test (S2PD)

The primary outcome of this study is the return of sensation 12 months after nerve injury, assessed using the S2PD, measured in millimeters. S2PD is the most widely used test to evaluate sensory function in the fingers [7]. The S2PD test evaluates tactile spatial acuity i.e. the ability to distinguish between two separate points of contact on the skin. The S2PD test, initially described by Weber in 1834, and later modified by Moberg [7] is performed using the Mackinnon-Dellon Disk-Criminator™ by applying two pins longitudinally over the radial and ulnar sides of the fingertip, with distances ranging from 0 to 25 mm. The minimum distance at which an individual can accurately distinguish between one or two points is recorded as the S2PD value. The test will be conducted in a standardized manner, ensuring that the pins are applied with just enough pressure to cause skin blanching [8], as excessive force may stimulate other receptors rather than mechanoreceptors responsible for pressure sensation [9, 10]. The injured finger is examined, as well as the corresponding finger on the uninjured hand for comparison. A correct response in seven out of ten random applications is required for a valid measurement.

Classification of sensory recovery according to the Mackinnon-Dellon scale [11], modified from the Highet classification, will be used. Sensation is classified as: Poor = >15 mm, Good = 7–15 mm, Excellent = 2–6 mm. The test and its validity have been questioned [12, 13].

### Secondary outcomes

Secondary outcomes will be collected at inclusion, 3 weeks, 3, 6 and 12 months after injury.

### Active range of motion (AROM)

The range of motion of finger joints will be measured as degrees of motion in MCP, PIP, and distal interphalangeal (DIP) joints. A finger Goniometer will be used for measurements [14, 15] and the degrees of motion of the three finger joints will be summed. The injured finger and the corresponding finger on the uninjured hand will be measured. The measurement technique will adhere to the Swedish hand surgery quality registry (HAKIR) measurement manual [16]. Finger stiffness is a common complication of any finger injury.

### Semmes–Weinstein Monofilament test, pocket version (SWM)

This test assesses cutaneous sensory perception threshold and is widely used to evaluate protective sensation recovery after nerve injury1 [17]. Two versions of the test exist: the original version, which comprises 20 monofilaments of varying thicknesses, and a compact pocket version that uses five monofilaments. We will use the pocket version, and all data are presented according to the five monofilament categories. The monofilaments are applied perpendicularly to the hand and fingers (digit I, II, V, and the hypothenar region). Pressure is applied until the filament bends, indicating sufficient force [7, 8]. The injured finger and the corresponding finger on the uninjured hand will be examined.

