## Statistical methods

### Statistical methods for primary and secondary outcomes {20a}

Primary outcome is a dichotomous outcome that will be presented as proportions of patients obtaining return of 2PD < 10 mm 1 year after injury, presented with 95% confidence interval, and proportions between groups will be compared with Chi^2^ analysis.

All numerical values will be tested for normality by Shapiro–Wilk’s test.

We assume normality/parametric data for age, AROM, and grip strength. Results are presented as numerical values on an interval scale. Central tendencies of data will be described as means with their corresponding standard deviation, and comparisons between groups will be performed with Student’s *t*-test or repeated measures ANOVA.

Categorical data will be presented as proportions and compared by Chi^2^ analysis, unless Fisher’s exact test is demanded due to expected small numbers. Ordinal data will be presented as medians and interquartile range (IQR), and Mann–Whitney *U*-tests or Wilcoxon’s test used for comparisons between groups.

We assume a skewed distribution for time to injury, sick leave, and PROMs, which will be presented as medians with IQRs and compared by Mann–Whitney *U*-tests or Wilcoxon’s test.

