### Methods in analysis to handle protocol non-adherence and any statistical methods to handle missing data {20c}

The main outcome in the final analysis will be presented according to the intention to treat principle. No imputation will be performed. Complications will be handled with an as-treated analysis.

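### The monofilament test sites contradict the eligibility criteria and the section's own last sentence, and the five categories leave no stated level for a finger that feels no filament

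*Protocol article*

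**What the plan says.** All of this is in the protocol article.

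- **Instrument and reporting.** The SWM section chooses "a compact pocket version that uses five monofilaments" and adds that "all data are presented according to the five monofilament categories". Table 1 gives the recorded unit as the filament, at 3 weeks and at 3, 6 and 12 months.
- **Sites.** The same section has the filaments "applied perpendicularly to the hand and fingers (digit I, II, V, and the hypothenar region"). Its last sentence reads: "The injured finger and the corresponding finger on the uninjured hand will be examined".
- **Eligibility.** *Inclusion criteria* requires a single digital nerve injury at the level of the proximal or middle phalanx. *Exclusion criteria* rules out "Injury to the digital nerves in the thumb".
- **Analysis.** Under *Statistical methods for primary and secondary outcomes {20a}*, "Ordinal data will be presented as medians and interquartile range (IQR"), with Mann–Whitney or Wilcoxon tests between groups. Section {20c} says "No imputation will be performed".

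**The concern.** There are two separate problems.

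**Where the test is done.** The site list does not match the injuries this trial enrols, and the sentence that closes the section follows a different rule. A therapist who follows the list and one who follows the closing sentence would record different data for the same patient. Neither statement says which reading enters the group comparison. Neither gives the side of the finger, which matters because only one of the finger's two digital nerves is cut and the other side keeps its own nerve.

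**How the result is scored.** One category per filament covers every finger that feels at least one filament. A finger that feels none has the worst possible result and no filament to record. The trial enrols nerve lacerations, leaves them unrepaired in one arm and tests from 3 weeks, so this result is foreseeable. The handling of these fingers affects the comparison if they are unequally common in the two arms.

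**Working it through.** The plan gives no figure for this outcome to reproduce. The check is a comparison of the text, a count, and one illustration.

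**1. Sites against eligibility**

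| Site | Listed for SWM? | Can it be the injured site? | Reached by the last sentence? |
|---|---|---|---|
| Digit I (thumb) | yes | no, excluded | no |
| Digit II | yes | yes | if injured |
| Digit III | no | yes | if injured |
| Digit IV | no | yes | if injured |
| Digit V | yes | yes | if injured |
| Hypothenar region | yes | no, injury must be at a phalanx | no |

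Two of the four listed sites can never be injured, and two of the four eligible digits are not listed. The last sentence covers all four eligible digits. The two statements agree only when digit II or V is injured.

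**2. Count of levels.** With k filaments the result is the thinnest filament felt (k possibilities) or none felt (1). For k = 5 this is 5 + 1 = 6 ordered results, against five stated categories. By contrast, the two-point discrimination classification has an open-ended worst class (above 15 mm).

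**3. What the missing level could do (illustration only).** The documents give no distribution for SWM, so every rate here is assumed. Let q₀ and q₁ be the shares with none felt after surgery and after cast. Assume that fingers feeling some filament have the same distribution in both arms, and that t = 0.15 of them feel only the thickest. The Mann–Whitney quantity is P = Pr(surgery better) + ½ Pr(tie); 0.500 means no difference.

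- None felt kept as the worst rank: P = (1 − q₀)q₁ + ½q₀q₁ + ½(1 − q₀)(1 − q₁) = 0.5 + (q₁ − q₀)/2.
- None felt left blank, not imputed: the two remaining distributions are identical, so P = 0.500.
- None felt merged with the thickest filament: P = 0.5 + (1 − t)(q₁ − q₀)/2.

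| q₀ v q₁ | Kept as worst | Left blank | Merged (t = 0.15) |
|---|---|---|---|
| 0% v 5% | 0.525 | 0.500 | 0.521 |
| 2% v 10% | 0.540 | 0.500 | 0.534 |
| 5% v 20% | 0.575 | 0.500 | 0.564 |
| 10% v 30% | 0.600 | 0.500 | 0.585 |

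For example, with 5% v 20%, kept is 0.5 + 0.15/2 = 0.575 and merged is 0.5 + 0.85 × 0.075 = 0.564. Leaving these fingers blank does the most harm. Merging removes only the fraction t of the effect, here 15%. The fall to exactly 0.500 follows from assuming equal distributions among the responders. If repair also helped them, some difference would remain.

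**The case against.** The strongest reply is that the document never says a finger without response is left blank or discarded. The five categories are not defined in this article. The section cites measurement sources for the procedure, one of which the Mini Sollerman section identifies as the registry's manual for nerve injuries. Section {18a} also refers to a separate follow-up form. Any of these may code non-response, and none is shown. The sentence on imputation concerns missing data, whereas none felt is an observation that can be ranked last. This stands. A reader might infer that these patients drop out and that the comparison is biased, but the documents do not support that. The illustration depends on invented rates and on an assumed handling.

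A reader might also infer that injured digits III and IV go untested. They do not, because the section's last sentence has the injured finger examined whichever it is. Nor does any section say that thumb or hypothenar readings enter the group comparison.

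What the reply does not remove is what the text itself fixes. It assigns all data to five categories for a five-filament kit, and it prints a specific site list that this trial's eligibility criteria contradict. The article describes itself as the complete protocol. A general manual could supply a code for non-response, but it would not reconcile the site list with the injuries enrolled here.

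**Conclusion.** The point holds as an internal contradiction on the test site plus an incomplete scale.

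- **Site.** The list includes two sites that eligibility rules out, omits two eligible digits and conflicts with the section's last sentence. This rests on the text alone.
- **Scale.** Six ordered results are assigned to five categories. The gap is in this text. That patients would be lost, or the comparison pulled toward no difference, is a risk only. It requires that non-response is left blank or merged and that it is commoner after cast alone. It also takes SWM to be analysed as ordinal data, since the statistical section does not name it.

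No size can be given from the documents. SWM is a secondary outcome, though named in the abstract. The primary outcome and the sample size are unaffected.

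**What to change.** 1. Replace the site list with one outcome site: the fingertip on the injured nerve's side of the injured finger. Test the matching site on the uninjured hand as reference.
2. Score six ordered levels, from the thinnest filament felt to none felt, with none felt as the worst rank. State that it is an observed value, and keep these patients in the Mann–Whitney comparison.
3. If the cited manual or the follow-up form already has such a code, say so in the SWM section and drop the reference to five categories.

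The cost is a change of wording and one extra box on the form. Records are on paper, so any result already written as not felt can be coded to the sixth level. Recruitment is expected to run to the end of 2030, so most forms may still be ahead. Forms already completed should be checked for which site and side were tested.
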